## Study sites: The study will be conducted in four unions located in Sreepur Upazila within Gazipur district, located north to Dhaka. Two of the unions, namely Rajabari and Prohladpur comprising 55 villages with 15,530 households and an estimated 76,150 population will serve as intervention area. The other two unions Telihat and Barmi will be taken as control sites. They contain 53 villages with 19,898 households and an estimated 99,000 population. Local drug vendors, village practitioners, traditional healers, and licensed government, private or NGO health service providers provide the curative health services in these sites.

## Study populations

1. Care takers of the children aged 6 months to 5 years with a prevalent case of diarrhea at the

time of the household surveys (within the past 2 weeks). Within each site a systematic household

survey will be completed for the identification of any child 6 months to 5 years who has a

prevalent case of at least 2 days duration.

2. Health Care Providers

1. NGO licensed “sub-assistant community medical officers (SACMOs)
2. Private sector, unlicensed providers: village practitioners and traditional healers

There are eight SACMOs and one medical officer posted at static and satellite clinics per two unions. Within each site a census will be carried out to enumerate all private sector providers by type. 10 of each type will be randomly selected to complete in-depth interviews.

## Intervention Package:

- Training/orientation on diarrhea case management
- Follow-up health provider support

ICDDR,B will first train the trainers, i.e. the NGO health care providers who will implement the intervention package. These individuals will then conduct the training and support of other NGO staff and private unlicensed providers.

[note: we would have liked to include licensed providers, but the #s are insufficient]

The training/orientation materials to be used are summarized in the box below:

###### Orientation package/training program

For DSK Health care providers (MBBS & SACMO): provided by ICDDR,B study staff

- Refresher course and up-date on WHO/UNICEF guidelines for treatment of childhood diarrhoea
- Training videos (docu-drama)
- Orientation/training materials (zinc babohar nirdeshika)
- Frequently asked questions booklet
- Follow-up support

For 1st line community health care providers (Village practitioner, drug venders, traditional healers): provided by DSK SACMO trainers

- Orientation/training materials (flip chart, zinc babohar nirdeshika)
- Training videos (docu-drama)
- Zinc commercial (mass media campaign)
- Refresher training and up-date on WHO/UNICEF guidelines for treatment of childhood diarrhea
- Frequently asked questions booklet
- Follow-up support

## The training provided by the NGOs will be done through quarterly meetings and follow-up sessions with village practitioners throughout the unions. This work will be done by Sub-Assistant Medical Officers (SACMOs). The SACMOs are graduates of diploma courses at government medical schools. This course includes three full years of study with an additional one year internship. SACMOs are licensed practitioners and are generally used to manage primary health care of patients.

## In each union covered by DSK, there are at least two SACMOs who have specialty training and experienced in the training of the village practitioners. Monitoring of the SACMOs will be done in accordance with the pre-existing management practice of DSK. DSK will adopt and integrate the intervention of appropriate diarrhea case management into an existing package of services.

## Sample Size Calculation and Outcome Variable(s)

## Sample size estimation for Survey

To detect a 50% increase in zinc usage in childhood diarrhoea in the intervention area, sample size was calculated using the following formula:

(Zα/2 +Zβ)2 [p (1-p)]X 2 X C

n =

d2

(1.64 +1 .28) 2 [.15 (1-.15)]X 2 X 1.5

=

(.075) 2

8.53 (.1275) X 2 X 1.5

= = 580 per group

.005625

where,

n = sample size, (Zα/2 +Zβ)2 = (1.64 + 1.28)2 = 8.53 (1 sided value at 95% confidence level and 90% power), p=.15 (baseline prevalence of zinc usage), d=.075 (50% increase in zinc usage after intervention), C = 1.5 (allowing an unknown cluster sampling design effect).

Given the target of 20 children per village, 29 randomly selected villages per group will be included.

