# Scaling up of Zinc:

Zinc scaling up efforts in Bangladesh focus on collaboration among ICDDR,B, the Ministry of Health and Family Welfare, ACME Laboratories and many other public and private sector organizations. The aim of this collaboration is to provide zinc treatment for diarrhoea on a national scale, targeting the entire under-five year-old population of Bangladesh. It has been estimated that zinc treatment could save the lives of up to 50,000 children per year in Bangladesh alone (12).

At present, the SUZY project has adopted the following scale-up strategies:

1. A mass media campaign
2. Provider promotion through ACME sales representatives
3. Orientation sessions with licensed providers
4. Training workshops for village doctors
5. Integration of zinc treatment into IMCI protocols (public sector)

The primary emphasis has been on reaching private providers through existing private sector channels. Thus far, we have not worked closely with the NGO sector. This could be an important,

additional strategy to further increasing zinc coverage across Bangladesh, in particular in communities highly reliant upon NGO services.

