**Rationale:**

In order to reach all children with diarrhoea, zinc treatment will need to be introduced and sustained within public, NGO and private service delivery systems. To improve zinc coverage, the Ministry of Health and Family Welfare (MOHFW) has initiated a program within the public sector that aims to distribute zinc, free of charge as a treatment of childhood diarrhea. However, a large population of the country, mostly the poor are served by NGO health services. Plan International, Bangladesh has been working for many years with children and families in some of the poorest communities, with aim of improving the quality of their lives, including their health. Across Bangladesh Plan works with 30 partner NGOs who provide community based services. These NGOs are highly respected within the communities they work, both among the general population and health providers. Whether these NGOs can significantly impact the diarrhoea treatment practices of private providers is unclear and should not be assumed. Past work carried out by the SUZY team with NSDP service providers plus local community sensitization and zinc promotion was not successful in improving zinc treatment coverage. The Plan model of having NGOs work with local providers is an alternative that deserves attention and validation of impact.

In Bangladesh, health seeking for childhood diarrhoea is dominated by utilization of private sector providers (18). Unlicensed providers (village doctors, drug sellers, and homeopaths) comprise more than 90% of the preferred source of care when help is sought.

The proposed study will be carried out in a rural community, where Dushtho Sasthya Kendra (DSK) [intervention area] and Ganosasthyo Kendra (GK) [control area], two partner NGOs of Plan International provide primary health care services along with other programs in Gazipur district, located north of Dhaka.

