The proposed study will assess the impact of a zinc scale up intervention package that entails strong and sustained NGO-private sector collaboration. The aim is to build upon the existing mass media and provider promotion campaigns already implemented in Bangladesh, in the hope that this additional collaboration will maximize zinc treatment coverage for acute childhood diarrhoea (ACD). The impact of the zinc scale up package on inappropriate prescription/sale of antibiotics will also be assessed. The proposed study will assess the impact of a zinc scale up intervention package that entails strong and sustained NGO-private sector collaboration. We will determine whether the effort and expense of scaling up specifically with NGOs provides value added to the nation-wide programs described above as well as other changes to the public health system.

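### The stated 90% power is not established for the between-area comparison, because the 7.5-point target is defined as a rise in the intervention area with no term for change in the control area

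*Protocol*

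**What the plan says.** Under Sample size estimation for Survey, the protocol states its target as follows: "To detect a 50% increase in zinc usage in childhood diarrhoea in the intervention area, sample size was calculated using the following formula". The inputs are given as "p=.15 (baseline prevalence of zinc usage), d=.075 (50% increase in zinc usage after intervention", with a design effect of 1.5 and a "1 sided value at 95% confidence level and 90% power". The result is 580 per group, in 29 villages per group. No control-area rate at endline and no control-area trend appears.

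The Study Design paragraph describes a controlled before-after study with an equivalent control area. The Rationale puts the question as an increment: "We will determine whether the effort and expense of scaling up specifically with NGOs provides value added to the nation-wide programs described above".

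The background describes national activity on zinc. Scaling up of Zinc lists several strategies, starting with "A mass media campaign", and also sales-force promotion, orientation of licensed providers and village-doctor training. The Rationale adds that the health ministry "has initiated a program within the public sector that aims to distribute zinc, free of charge as a treatment of childhood diarrhea". Neither section confines this activity to the two intervention unions. The endline survey follows the baseline by six months (Measurement/Data collection tools).

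**The concern.** A rise after intervention in one area and a difference between two areas are the same quantity only if the other area does not move. The sizing defines its effect in the first way, while the study asks its question in the second. Any rise in control-area coverage between the surveys comes straight off the net effect if the intervention area only reaches 22.5%. The control area is there to remove such a trend, so the sizing should say what it assumes about it.

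The Rationale wants the result to show whether the effort and expense of working through NGOs is worthwhile. If the intervention area reached the planned 22.5% while control use also rose, the study could have well under 90% power to show added value. A reader relying on the stated power would then give a non-significant result more weight than it deserves.

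**Working it through.** **Inputs from Sample size estimation for Survey.** p = 0.15, so p(1 − p) = 0.1275; d = 0.075; z values 1.64 (one-sided 5%) and 1.28 (90% power); C = 1.5; n = 580 per group.

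**Assumed, not in the protocol.** Control-area endline coverage of 15, 16, 17 or 18%. For the difference in change, also a 15% baseline in both areas, four independent samples of 580 and the same design effect in each.

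**1. The plan's figure.** The section gives "Zα/2 +Zβ)2 = (1.64 + 1.28)2 = 8.53". Then n = 8.53 × 0.1275 × 2 × 1.5 / 0.005625 = 580. The figure reproduces.

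**2. What the 90% refers to.** The effective size per group is 580/1.5 = 386.7. With the plan's variance, SE = √(2 × 0.1275/386.7) = 0.0257, and power = Φ(0.075/0.0257 − 1.64) = 90%. This is a two-sample contrast of 22.5% with 15%, with the variance taken at 15% in both groups.

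**3. Endline contrast, variance at both rates, intervention area at 22.5%.** SE = √{[c(1 − c) + 0.225 × 0.775]/386.7} and power = Φ[(0.225 − c)/SE − 1.645], where c is control-area coverage at endline.

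**4. Difference in change, same rates.** The two baseline samples add 2 × 0.1275 to the variance: SE = √{[2 × 0.1275 + c(1 − c) + 0.225 × 0.775]/386.7}.

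**5. Net gain of 7.5 points over the risen control rate, endline contrast.** The intervention rate is c + 0.075, and the variance is taken at c and c + 0.075.

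| Control at endline (assumed) | Net effect if intervention reaches 22.5% | Step 3: endline | Step 4: difference in change | Step 5: net 7.5 points, endline |
|---|---|---|---|---|
| 15% | 7.5 points | 85% | 63% | 85% |
| 16% | 6.5 points | 74% | 52% | 84% |
| 17% | 5.5 points | 61% | 42% | 83% |
| 18% | 4.5 points | 47% | 32% | 81% |

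For example, in step 3 at c = 0.18, SE = √[(0.1476 + 0.1744)/386.7] = 0.0289 and power = Φ(0.045/0.0289 − 1.645) = 47%.

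**6. Difference detectable with 90% power at 580 per group, control at 15%.** Solve δ = (1.645 + 1.282) × SE(δ), with the intervention area at 0.15 + δ.
- Endline contrast: δ = 0.082, since SE = √[(0.1275 + 0.1783)/386.7] = 0.0281 and 2.927 × 0.0281 = 0.082. That is about 8.2 points.
- Difference in change: δ = 0.113, since SE = √[(0.3825 + 0.1938)/386.7] = 0.0386 and 2.927 × 0.0386 = 0.113. That is about 11.3 points.

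**The case against.** The formula is a two-sample formula, the result is stated per group, and the control area is called equivalent. On that footing 15% could be a common starting rate and 7.5 points the intended between-group difference. The label is only "p=.15 (baseline prevalence of zinc usage"; the text never says it is the intervention area's own rate. This stands: that reading is natural from the wording around it, but it is not stated. It does not remove the point, because the section still defines d as a rise in the intervention area and gives no control rate.

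A reader might infer that the protocol itself expects control-area use to rise. It does not say so. National programmes make a rise plausible, but no section gives a trend or their level of activity in these unions. The Rationale calls the mass media and promotion campaigns already implemented, so part of their effect may be in the 15%. It also reports that earlier provider work with local zinc promotion did not improve coverage.

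A reader might also take the steep loss of power as certain. It holds only if the intervention area stops at 22.5%. With a net 7.5 points the loss from a control rise is small. If the 50% were a relative gain over the risen control rate, endline power would be about 87, 90 and 91% at control rates of 16, 17 and 18%. The section does not adopt either reading.

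Finally, a reader might conclude that a flat control rate would secure 90%. It would not: with control at 15%, power is about 85% at endline and about 63% for the difference in change.

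**Conclusion.** The point holds as a mismatch between the effect that was sized and the comparison the study is meant to make. The protocol fixes d as a rise in the intervention area from a 15% baseline and leaves out the control area, so its 90% power is not established for value added over the national programmes.

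The size depends on the contrast and on an assumed control rate. With the intervention area at 22.5% and control between 15 and 18%, power runs from about 85% down to 47% at endline, and from about 63% down to 32% for the difference in change. On the more favourable reading of a net 7.5 points, endline power runs only from about 85% to 81%. The difference-in-change figures also rest on independent samples with a common design effect of 1.5. The documents do not show that control use will rise, so the lower figures are scenarios and not predictions.

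**What to change.** In Sample size estimation for Survey:

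1. Define d as the net difference between the intervention and control areas, and say whether the test is the endline contrast or the difference in change from baseline.
2. State the assumed control-area coverage at endline under the ongoing national programmes, labelled as an assumption.
3. Replace the single 90% figure with the power at 580 per group for the chosen contrast, with the variance at both rates, across a short range of control rates. If the intervention area is taken to reach 22.5%, the entries for control at 15, 16, 17 and 18% are about 85, 74, 61 and 47% (endline) or 63, 52, 42 and 32% (difference in change). If 7.5 points is meant as net, the endline entries are about 85, 84, 83 and 81%.
4. State the net difference detectable with 90% power at 580 per group with control at 15%: about 8.2 points at endline, or about 11.3 points for the difference in change.

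The cost is a few sentences and a small table. No children, villages or fieldwork are added. The only downside is a stated power less favourable than 90%.

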| **Targeted Population (Check all that apply):**  No ethnic selection (Bangladeshi)  Bangalee  Tribal group | | Expatriates  Immigrants  Refugee | | | | |
| **Consent Process (Check all that apply):**  Written  Oral  None | | X Bengali Language  English Language | | | | |
| **Proposed Sample Size:** 1160 in baseline and end line will be interviewed  Sub-group (Name of subgroup (e.g. Men, Women) and Number   | Name | Number | Name | Number | | --- | --- | --- | --- | | (1) households | 1160 | (3) NGO providers | 8 | | (2) private sector providers | 20 |  |  |   Total sample size: 1188 | | | | | | |
| **Determination of Risk: Does the Research Involve (**Check all that apply**):**   | Human exposure to radioactive agents?  Fetal tissue or abortus?  Investigational new device?  (specify:      )  Existing data available from Co-investigator | Human exposure to infectious agents?  Investigational new drug  Existing data available via public archives/sources  Pathological or diagnostic clinical specimen only  Observation of public behaviour  New treatment regime | | --- | --- | | | | | | | |
| **Could the information recorded about the individual if it became known outside of the research:**   | Yes  X | No | Is the information recorded in such a manner that study participants can be identified from information provided directly or through identifiers linked to the study participants? | | --- | --- | --- | | Yes | No  X | Does the research deal with sensitive aspects of the study participants’ behaviour; sexual behaviour, alcohol use or illegal conduct such as drug use? |  | Yes | No  X | Place the study participants at risk of criminal or civil liability? | | --- | --- | --- | | Yes | No  X | Damage the study participants’ financial standing, reputation or employability, social rejection, lead to stigma, divorce etc.? | | | | | | | |
| **Do you consider this research (Check one):**  Greater than minimal risk X No more than minimal risk  Only part of the diagnostic test  Minimal Risk is "a risk where the probability and magnitude of harm or discomfort anticipated in the proposed research are not greater in and of themselves than those ordinarily encountered in daily life or during the performance of routine physical, psychological examinations or tests. For example, risk of drawing a small amount of blood from a healthy individual for research purposes is no greater than the risk of doing so as a part of routine physical examination". | | | | | | |

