**Research Design and Methods**

Describe in detail the methods and procedures that will be used to accomplish the objectives and specific aims of the project. Discuss the alternative methods that are available and justify the use of the method proposed in the study. Justify the scientific validity of the methodological approach (biomedical, social, or environmental) as an investigation tool to achieve the specific aims. Discuss the limitations and difficulties of the proposed procedures and sufficiently justify the use of them. Discuss the ethical issues related to biomedical and social research for employing special procedures, such as invasive procedures in sick children, use of isotopes or any other hazardous materials, or social questionnaires relating to individual privacy. Point out safety procedures to be observed for protection of individuals during any situations or materials that may be injurious to human health. The methodology section should be sufficiently descriptive to allow the reviewers to make valid and unambiguous assessment of the project.

**Study Design:** This will be controlled before-after (CBA) study. An equivalent control area will be included in the study. The objective is to document changes in zinc and antibiotic as well as anti-diarrhoeal usage in childhood diarrhoea following a scale-up intervention package delivered by a local NGO to local private providers. This will include sensitization, training and follow-up support. Impact will be assessed in terms of changes in zinc coverage and antibiotic use among households in the catchment population served by these providers.

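### The 580 per group powers a comparison of two proportions; for the controlled before-after contrast it gives about 66% power on the protocol's own inputs, not 90%

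*Protocol*

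**What the plan says.** The Protocol's section on sample size estimation for the survey begins "To detect a 50% increase in zinc usage in childhood diarrhoea in the intervention area, sample size was calculated using the following formula". The inputs are "p=.15 (baseline prevalence of zinc usage"), "d=.075 (50% increase in zinc usage after intervention"), "C = 1.5 (allowing an unknown cluster sampling design effect") and normal quantiles of 1.64 and 1.28, described as "1 sided value at 95% confidence level and 90% power". The result is 580 per group, to be met with 29 villages of 20 children each.

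Under Study Design the protocol states: "This will be controlled before-after (CBA) study". It adds an equivalent control area and says that impact will be judged by changes in zinc coverage and antibiotic use. The Rationale says that the study will determine whether working through NGOs adds value over the nationwide programmes. Under Measurement/Data collection tools, an endline survey of cases active at that time follows six months after baseline.

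Data Analysis lists coverage, changes in coverage, and crude relative risks with 95% confidence intervals. It does not name a contrast of area by time. The face sheet says "1160 in baseline and end line will be interviewed" and then "Total sample size: 1188".

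**The concern.** The factor of 2 in the formula fits one comparison of two independent proportions: before against after in one area, or one area against the other at a single time. Neither answers the question the study sets itself.

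- A before-after comparison in the intervention area alone cannot separate the NGO package from the mass media campaign, sales promotion and public-sector supply described in the background. It also leaves the control area out of the powered comparison.
- An endline comparison of areas alone ignores the baseline survey. It assumes that two pairs of unions, with no random allocation described, started level.

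The contrast that uses the whole design is the change in the intervention area minus the change in the control area. Its variance is the sum of four terms, and the sample size section makes no allowance for the extra two. At stake is how a null result is read. A study believed to have 90% power would count as fairly strong evidence against the NGO model, which it would not be if the controlled contrast has much less.

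**Working it through.** **Inputs.** From the sample size section: p = 0.15, d = 0.075 (so 0.225 after the intervention), design effect C = 1.5, one-sided 5%, 90% power, n = 580. From the design: two areas by two rounds, so four cells, taken as 580 each.

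**1. The protocol's own figure.** n = (1.64 + 1.28)² × 0.1275 × 2 × 1.5 / 0.005625 = 579.8. The 580 reproduces.

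**2. Standard error and power for the two-cell comparison.** SE = √(2 × 0.1275 × 1.5 / 580) = 0.0257. Power = Φ(0.075/0.0257 − 1.645) = 89.9%. With 1.96 in place of 1.645 it is 83.2%.

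**3. Difference in changes, protocol variance in all four cells.** SE = √(4 × 0.1275 × 1.5 / 580) = 0.0363, larger by a factor of √2 = 1.41. The ratio 0.075/0.0363 is 2.065.
- One-sided: Φ(2.065 − 1.645) = 66.3%.
- Two-sided: Φ(2.065 − 1.96) = 54.2%.

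**4. Difference in changes, variance at 22.5% in the changed cell.** Sum of variances = 3 × 0.1275 + 0.225 × 0.775 = 0.556875. SE = √(0.556875 × 1.5 / 580) = 0.0380, which is 48% above 0.0257. The ratio 0.075/0.0380 is 1.976.
- One-sided: 63.0%.
- Two-sided: 50.7%.

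**5. Detectable difference at 90% power, 580 per cell.** This is (z for alpha + 1.282) × SE.
- Protocol variance: 2.926 × 0.0363 = 10.6 points one-sided; 3.242 × 0.0363 = 11.8 points two-sided.
- Letting the changed cell's variance follow the effect: 11.3 and 12.6 points.

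**6. n per cell for 90% power at d = 0.075 (for scale only).** One-sided, about 1,165 (protocol variance) to 1,272 (step 4 variance). Two-sided, about 1,429 to 1,560.

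**7. Sensitivity to resurveying the same villages (assumption).** C = 1.5 with 20 children per village implies an intracluster correlation of 0.5/19 = 0.026. If village effects correlate r between rounds, C is replaced by 1.5 − 20 × 0.026 × r.

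| r | One-sided power | Two-sided power |
|---|---|---|
| 0 (independent rounds) | 63-66% | 51-54% |
| 0.5 | 70-74% | 59-62% |
| 1.0 (extreme) | 79-82% | 69-73% |

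The lower end of each range uses the step 4 variance, the upper end the protocol variance.

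**8. Sensitivity to a rise in the control area.** If control coverage reaches 20% to 22.5% at endline and the intervention area is 7.5 points higher, power under independent rounds is 59% to 58% one-sided and 47% to 45% two-sided.

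**9. Face sheet.** 1160 + 20 + 8 = 1188 counts one household round. Two rounds make 580 × 2 × 2 = 2,320 household interviews.

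**The case against.** The best defence is that the protocol never attaches its 90% to a difference in changes. The sample size section declares an increase in the intervention area as its target, the first hypothesis speaks of an increase within the NGO catchment population, and Data Analysis names no test of area by time. For a before-after comparison in one area the formula is appropriate and the sum is right. This stands to the extent that there is no arithmetical error. The defect is a mismatch between the contrast that was sized and the one that the design and Rationale call for.

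A reader might infer that the true power is 51%, little better than an even chance. The documents do not support that as the lead figure. The calculation is stated as one-sided with 0.15 × 0.85 throughout. Changing only the number of cells gives 66%. The step to 63% comes from a different variance in one cell, which on its own would also lower the two-cell power, and the step to 51% comes from changing sidedness as well. The two-sided figure is still relevant, because the formula symbol is written as Zα/2 and 95% confidence intervals are planned, but it is a second issue.

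Independence between rounds is also an assumption. The protocol does not say whether villages are redrawn. With 29 taken from 55 or 53, even a fresh draw would be expected to share about 15 or 16 villages (29²/55 and 29²/53). Some gain in power is therefore plausible, but no case computed reaches 90%.

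Finally, one might read 1160 as the total over both rounds, or 290 per cell, with power of 40% one-sided. That reading is not needed: 1160 at each round agrees with 580 per group and with 29 × 20. The face sheet is ambiguous and does not show that a smaller study was intended.

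**Conclusion.** The point holds as a mismatch between sample size and design. The 580 per group is correct for comparing 15% with 22.5% in two samples, but it does not give 90% power for the change in the intervention area net of the change in the control area. On the protocol's own inputs, one-sided power for that contrast is about 66%, or about 63% with the variance at 22.5% in the changed cell. Against two-sided 95% confidence intervals it is about 54% or 51%. These figures rest on 580 per area per round, a design effect of 1.5, flat control coverage and independent rounds. Resurveying the same villages could raise the one-sided figure to about 70-82% for assumed between-round correlations of 0.5 to 1.0. A rise in control coverage would lower it somewhat.

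**What to change.** In the sample size section:

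- Name the difference in changes (intervention minus control) as the powered contrast, with n per cell = (z for alpha + z for power)² × C × (sum of the four p(1−p) terms) / d².
- Keep 580 per area per round. Replace the 90% with the power for this contrast: about 63-66% one-sided or 51-54% two-sided under independent rounds.
- Give the difference detectable with 90% power: about 11 points one-sided, 12-13 two-sided.
- Say whether the same villages are surveyed in both rounds. If they are, state the between-round correlation assumed and the power that follows.

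On the face sheet, state that 1160 is the number per round, which makes 2,320 household interviews in total.

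The cost is protocol wording and a less favourable power statement. No extra enrolment or fieldwork is asked for.

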## Data Analysis

Describe plans for data analysis. Indicate whether data will be analyzed by the investigators themselves or by other professionals. Specify what statistical software packages will be used and if the study is blinded, when the code will be opened. For clinical trials, indicate if interim data analysis will be required to monitor further progress of the study.

The investigative team will carry out the data analysis. Data entry and general management will be done by Data Resources and Surveillance Unit of the Division. Data will be entered and analyzed using SPSS version 12.0. Absolute counts, proportions, and means with 95% confidence interval will be calculated. These and regression analysis will be done using STATA version 9, cluster survey program, that accounts for potential within cluster homogeneity.

Based upon the household surveys, the following outcomes will be calculated:

- Coverage: the proportion receiving zinc, ORS (zinc and ORS), and antibiotics or antidiarrhoeals and changes in coverage 6 months following the introduction of the intervention package.
- Equity: who is receiving zinc by age, gender and socioeconomic status
- For differences in categorical outcomes crude relative risks and 95% confidence intervals will be determined.

The provider interviews will be recorded and transcripts prepared. Qualitative responses will be sub-grouped by topic and response.

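### The stated 90% power gives both groups the 15% baseline variance; with 22.5% in the intervention group, 580 per group gives about 85% at the plan's one-sided 5% level

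*Protocol*

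**What the plan says.** The protocol's section on sample size estimation for the survey gives one calculation, for zinc use, with its error rates and proportions listed together as "1 sided value at 95% confidence level and 90% power), p=.15 (baseline prevalence of zinc usage), d=.075". In detail:

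- The z values are described as "Zα/2 +Zβ)2 = (1.64 + 1.28)2 = 8.53 (1 sided value at 95% confidence level and 90% power". The symbol is the two-sided one; the number and the words are one-sided.
- The starting proportion is "p=.15 (baseline prevalence of zinc usage" and the target difference is "d=.075 (50% increase in zinc usage after intervention". The alternative is therefore 15% against 22.5%.
- The numerator is "8.53 (.1275) X 2 X 1.5". Here 0.1275 is 0.15 × 0.85, the 2 stands for two groups and 1.5 is the design effect.
- The result is 580 per group, to be found in 29 villages of 20 children.

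The Data Analysis section says "Absolute counts, proportions, and means with 95% confidence interval will be calculated". It also plans unadjusted relative risks with intervals at the same 95% level for categorical outcomes. It does not mention a one-sided test or interval. The hypotheses are directional: an increase in zinc coverage, and a decrease in antibiotic and antidiarrhoeal use.

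**The concern.** The variance of a proportion depends on the proportion. At 22.5% it is 0.225 × 0.775 = 0.174375, which is 37% above the 0.1275 used (0.174375 / 0.1275 = 1.37). Using the baseline value for both groups understates the variance of the difference and so overstates power. The error is in the favourable direction because the expected shift is upward from a low proportion.

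Separately, the design is sized one-sided, while the analysis section describes results only through 95% confidence intervals, which are ordinarily two-sided. If a two-sided interval that excludes no effect is what will count as success, the design and the analysis use different error rates.

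At stake is the chance of missing the targeted effect on the outcome behind the first hypothesis. Those who approve or fund the study, and those who later interpret a null result, would take that chance to be 10% when it is larger.

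**Working it through.** **Inputs, all from the sample size section:** p1 = 0.15, d = 0.075, hence p2 = 0.225; z values 1.64 and 1.28; design effect C = 1.5; n = 580 per group.

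**1. Reproduce the plan's figure.**
n = (1.64 + 1.28)² × 0.1275 × 2 × 1.5 / 0.075² = 8.5264 × 0.3825 / 0.005625 = 579.8.
The stated 580 follows from its inputs. Unrounded z values give 582.3, so rounding plays no part.

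**2. Power as the plan computes it (baseline variance in both groups).**
SE = √(0.255 × 1.5 / 580) = 0.02568; 0.075 / SE = 2.920.
- One-sided 5%: Φ(2.920 − 1.645) = 89.9%
- Two-sided 5%: Φ(2.920 − 1.960) = 83.2%

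**3. Power with each group's own variance.**
p1(1−p1) + p2(1−p2) = 0.1275 + 0.174375 = 0.301875, against 0.255 in the plan (ratio 1.18).
SE = √(0.301875 × 1.5 / 580) = 0.02794; 0.075 / SE = 2.684.
- One-sided 5%: Φ(2.684 − 1.645) = 85.1%
- Two-sided 5%: Φ(2.684 − 1.960) = 76.6%

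The version with pooled variance under the null gives 84.9% and 76.3%, so the choice of approximation does not matter.

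| Variance used | One-sided 5% | Two-sided 5% |
|---|---|---|
| 15% in both groups (the plan) | 90% | 83% |
| 15% and 22.5% | 85% | 76-77% |

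**4. Scale of the shortfall.** For 90% power with the corrected variance, about 689-693 per group would be needed one-sided, or 846-852 two-sided (unpooled and pooled formulas). These figures show the size of the gap and are not a proposal to enlarge the survey.

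**5. Context: the before-after contrast.** The figures above are for two groups compared once, but the design is a controlled before-after study. Assume 580 per area in each round, independent samples, 15% in both areas at baseline, no change in the control area and a design effect of 1.5. The variance sum is then 3 × 0.1275 + 0.174375 = 0.556875, SE = √(0.556875 × 1.5 / 580) = 0.03795, and 0.075 / SE = 1.976. Power for a difference in changes of 0.075 is about 63% one-sided and 51% two-sided. The protocol does not state these assumptions.

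**The case against.** **The one-sided choice is open.** The text says "1 sided value at 95% confidence level and 90% power", and the hypotheses are directional, so a one-sided 5% design is coherent. This stands. The Zα/2 symbol is a wrong label that changes no number, and it should not be called a formula error that inflated the power.

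**The intervals need not decide anything.** A reader might infer that the true power is 77% because 95% intervals are planned. The documents do not go that far. They do not call the intervals two-sided, nor do they make excluding no effect the decision rule, and ordinary 95% intervals can be reported beside a one-sided test. The sidedness of the final test may also be set in an analysis plan that is not shown. So 76-77% is conditional. What remains is that the one document at hand is sized one-sided and says nothing about one-sided inference where it describes the analysis.

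**Using p(1−p) for both groups is a common simplification, and the loss is modest.** This is partly right. Power stays above 80% on the plan's own terms, and the design effect is itself described as unknown. At an illustrative design effect of 1.25, SE = √(0.301875 × 1.25 / 580) = 0.0255 and one-sided power is Φ(2.940 − 1.645) = 90%. But the plan chose 1.5, and a larger value would lower power. Uncertainty in one input does not justify a variance that contradicts the plan's own alternative.

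**The before-after contrast matters more.** If the difference in changes is primary, its power replaces the two-group figure. That is a reason to state which contrast the power refers to. It does not support the 90%.

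**Conclusion.** The point holds as a misstated power. With the plan's own proportions, design effect and one-sided 5% level, 580 per group gives about 85% power for a two-group comparison, so the chance of missing the targeted effect is about 15%, not 10%. This needs no assumption beyond the normal approximation.

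The sidedness point is a mismatch between sections plus a mislabelled symbol. If two-sided 95% intervals are the criterion, which is the ordinary reading but is not stated, power is 76-77% and the miss rate is 23-24%. The 90% fails on either reading.

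Two stronger inferences are not supported. The arithmetic behind 580 is not wrong, since it reproduces from its inputs. Nor does the finding by itself require more children, because 85% is a usable power if it is stated honestly.

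**What to change.** In the sample size section:

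- Replace 2p(1−p) with p1(1−p1) + p2(1−p2), using 15% and 22.5%.
- Make the z symbol match the value used: Zα if 1.64 stays, or Zα/2 with 1.96.
- Restate the power of 580 per group for a two-group comparison as about 85% (one-sided 5%) or 76-77% (two-sided 5%).
- Say which contrast the power refers to. If the difference in changes between areas is primary, give that figure with its assumptions instead.

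In the Data Analysis section, state the same sidedness as in the design, and say whether the 95% intervals are the criterion or descriptive.

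The cost is a few lines of protocol text and a less favourable stated power. No change in sample size or fieldwork is required.
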